## Abstract

**Background:**

Diabetes is a serious chronic disease. Medical treatment and good psychosocial support are needed to cope with acute and long-term effects of diabetes. Self-management is a large part of diabetes management, with healthcare providers playing a supportive role. Young adults with type 1 diabetes are of special interest as they tend to have higher mean glycosylated haemoglobin values than other patients with type 1 diabetes, and they often miss visits in traditional diabetes care. A well-designed virtual solution may improve a range of measures (e.g. glycaemic control and perceived health) and reduce hospitalisations.

**Method:**

This randomised controlled trial with a control group using a wait list design will recruit 100 young adults from a hospital in Sweden. All participants will receive usual diabetes care besides the virtual clinic. The primary objective is to evaluate the effect of a virtual diabetes clinic on glycaemic control, treatment satisfaction and quality of life in young adults (aged 18–25 years) with type-1 diabetes. The secondary objective is to determine the effects of virtual care on the patient experience.

**Discussion:**

Virtual tools are becoming increasingly common in healthcare; however, it remains unclear if these tools improve diabetes self-management. The results of this study will build understanding of how healthcare providers can use a virtual clinic to improve diabetes self-management.

**Trial registration:**

Current controlled trials: ISRCTN, number: 73435627, registered 23 October 2019. 10.1186/ISRCTN73435627

## Background

Diabetes is a common and serious chronic disease that may have severe complications and is a cause of premature death [1, 2]. Diabetes is an ever-present condition characterised by a constant struggle and by feelings of constraint, of fear, shame and of being alone, but also by courage, by a sense of trusting one’s own abilities and by closeness with family, friends and others with diabetes [3, 4].

Self-management could be challenge and difficult to maintain for many diabetes patients. Patients describe their everyday life as a balancing act between high and low blood sugar concentrations, between diet and exercise and desire and demands [3, 4]. It is possible to live a good life with diabetes, but this is demanding. Self-management is a crucial part of diabetes management, especially for those with insulin treatment. Data obtained from the National Diabetes Registry in Sweden showed that many people with diabetes have difficulty achieving the recommended glycaemic control; in particular, young people find it difficult to manage their daily treatment requirements to achieve good blood glucose values [5, 6]. The reason for this is partly unknown; factors such as genetic variations, fear of hypoglycemia, stress, depression and lack of knowledge may be contributing factors [3, 7–9]. In addition, studies have shown that depression is two to four times more common in people with diabetes compared with the general population [10]. The self-management is often unsatisfied with many missed doses to meals and snacks [11].

Professional diabetes care is crucial for the patient’s ability to manage their diabetes. This is facilitated through medical and technical guidance and support according to the individual’s needs [12]. Through the rapid development of advanced treatment technology, higher demands are placed on diabetes caregiver in order to provide care, education, and support for patients with diabetes and their relatives [13]. Today, the number of personal diabetes visits is increasing and in combination with a lack of glycemic control and advanced diabetes technology, it often creates an overwhelming burden for traditional diabetes care [5, 6, 14]. The roles and responsibilities of healthcare professionals have also changed from one who ‘tells’ to one who ‘listens’, which highlights person-centred care compared with a conventional hierarchical approach [12]. This raises the question as to whether the diabetes care currently offered to patients living with diabetes is optimal.

Previous studies in this area have evaluated components of virtual clinics (e.g. mobile applications, SMS and computer-based diabetes care) as part of telemedicine. However, these studies did not focus on patient-centred virtual diabetes care. A recent literature review focused on telemedicine for diabetes that included 55 randomised controlled trials found that compared with conventional diabetes care, telemedicine improved treatment outcomes for patients with type-1 and type-2 diabetes [15]. That review found slightly better results for patients with type-2 diabetes; however, glycosylated haemoglobin (HbA1c) was reduced in patients with type-1 and type-2 diabetes. The discussion of the limitations of the review indicated that as the measure used was HbA1c, potential for improvements in other areas of diabetes management were not assessed (e.g. fear of hypoglycaemia or satisfaction with treatment). In another review focusing on type 1 diabetes and distal technologies (various electronic systems providing remote services) *telehealth*, such as telephone calls and video appointments, was the one technology that hitherto could prove similar or better glycaemic control with potential additional benefits, regarding costs, efficiency geographic barriers and convenience [16]. The need to assess other health parameters in addition to HbA1c, as well as conducting studies with higher methodological quality has been confirmed by other research [17, 18]. Moreover, previous research has not focused on the difficult group of young adults with type 1 diabetes. This group of patients is of special interest to try to reach with virtual diabetes care, as they have higher mean HbA_1_c values than other patients with type 1 diabetes. In addition, they often miss visits in traditional diabetes care. At the same time, they frequently have advanced technologies (e.g. insulin pumps and continuous or flash glucose monitoring systems), which provide in-depth data, able to share on-line with health care professionals, allowing detailed analysis and advice for diabetes care at a distance.

A potential low-cost intervention to support diabetes self-management could be through virtual diabetes clinics via a smartphone app. Virtual clinics increase the opportunities for people with diabetes to retain contact with” their” diabetes nurse or doctor, allowing for continuity of care and providing a sense of security for many patients. Principles specific to virtual diabetes care are that patients can communicate from their home environment and if needed, have opportunity for more frequent contact with healthcare providers using virtual clinics.

### Study aim

The primary objective of this study is to evaluate the effect of a virtual diabetes clinic on glycaemic control, treatment satisfaction and quality of life in young adults (aged 18–25 years) with type-1 diabetes. The secondary objective is to determine the effects of virtual care on the patient experience.

## Method/design

### Study design

This study will be a randomised controlled trial with a control group according to a wait list design.

### Participants and recruitment

The inclusion criteria for the study are people: with type 1 diabetes; aged 18–25 years; and registered at a single hospital in Stockholm, Sweden. Participants will be identified from the diabetes clinic patient register by the hospital staff. Exclusion criteria are duration of diabetes shorter than 1 year, a diagnosis of severe depression; eating disorders or other serious mental illness; alcohol/drug abuse; or severe diabetes complications. The diabetes nurse and/or physician will be the person who makes the decision whether the diabetic patient has compliance to be able to participate in the study. The study hospital’s outpatient diabetic reception is currently responsible for about 410 patients in the target age group. Written and verbal information about the study will be provided to patients who meet the above criteria. Written informed consent will be obtained from all participants.

Participants who meet the inclusion criteria, are willing to take part in the study and provide informed consent will be randomly allocated to either the intervention group or a wait-list control group. The primary outcome/end point will be glycaemic control; HbA1c, Time In Range and Time Below Range, Severe Hypoglycemia and Diabetic Ketoacidosis, respectively. Secondary outcomes will be treatment satisfaction, quality of life and patients’ experience of virtual care. All participants will receive usual diabetes care in addition to the virtual clinic.

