### Statistical analysis and power calculation

To detect a mean difference of 6 mmol/mol (standard deviation [SD] = 9) in HbA1c, it will be necessary to include at least 37 participants in each group (alpha 0.05, power 80%, two-sided test). Taking dropout rates into consideration, a total of 100 patients will be included in the study. Participants will be randomly assigned to either experimental or control group with a 1:1 distribution as per a computer-generated randomisation.

All analyses will be conducted on an intention-to-treat basis. The difference at the 6-month follow-up between the intervention and wait-list control groups (adjusted for values at baseline) will be analysed with a two-sided independent samples Student’s *t*-test with a 95% confidence interval. A *p*-value < 0.05 will be considered statistically significant. Mean (SD) values and 95% confidence intervals will be used to describe the sample. A secondary analysis of the primary endpoint will adjust for baseline characteristics. For independent samples, a Student’s *t*-test will be used when comparing two categories for interval or ratio data, and a Mann-Whitney U test will be used for ordinal data. When three or more categories are compared, analysis of variance will be used for interval or ratio data and the Kruskal-Wallis test will be used for ordinal data. Generalised estimating equation regression models will be used for comparisons within groups over the three time points. All statistical analyses will be performed with IBM SPSS Statistics.

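### Five separate measures carry the primary label while only HbA1c is powered, and the primary objective includes two domains classed elsewhere as secondary, so no single primary endpoint is defined

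*Protocol article*

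**What the plan says.** Four places in the protocol article bear on what the trial's primary question is.

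- **Participants and recruitment** gives the primary outcome: "The primary outcome/end point will be glycaemic control; HbA1c, Time In Range and Time Below Range, Severe Hypoglycemia and Diabetic Ketoacidosis, respectively". The next sentence reads: "Secondary outcomes will be treatment satisfaction, quality of life and patients’ experience of virtual care".
- **Study aim** sets a wider primary objective: "The primary objective of this study is to evaluate the effect of a virtual diabetes clinic on glycaemic control, treatment satisfaction and quality of life". The Method paragraph of the abstract says the same, and the opening of the Discussion restates the aim with the same three domains.
- **Statistical analysis and power calculation** sizes the trial on one measure: "To detect a mean difference of 6 mmol/mol (standard deviation [SD] = 9) in HbA1c", with "alpha 0.05, power 80%, two-sided test", giving 37 per group and 100 in total after an unstated allowance for dropout.
- **The same section** sets one threshold for all tests, "value < 0.05 will be considered statistically significant". It places the between-group comparison at 6 months and refers to the primary endpoint in the singular without saying which measure that is.

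**The concern.** The sections give three different accounts of the primary question: one measure (the power calculation), five measures (the outcome list) and three domains (the objective). Nothing in the article says whether the five measures form a composite, must all succeed, are ranked, or are led by HbA1c.

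The primary endpoint settles what the trial may claim. While it is open, a favourable result on one of the five could be presented as meeting the primary objective. A split result, such as better HbA1c with more time below range, has no planned reading. Treatment satisfaction and quality of life could be reported as primary by citing the aim, or as secondary by citing the outcome list.

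**Working it through.** **1. The plan's own figure.** Inputs from Statistical analysis and power calculation: difference 6 mmol/mol, SD 9, two-sided alpha 0.05, power 80%, 1:1 allocation.

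- Normal approximation: n = 2 × (1.960 + 0.842)² × (9/6)² = 2 × 7.85 × 2.25 = 35.3, so 36 per group.
- The t-test solution is 36.3, so 37 per group. This matches the stated number.
- Power by t-test is 80.8% with 37 per group and 91.0% with 50.

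The sample size is therefore right for HbA1c tested alone at the full 0.05.

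**2. Error rate if any one of the five counted as success.** This rule is an assumption used to size the issue. The article does not state it.

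- Two-sided rejections, independent tests: 1 − 0.95⁵ = 22.6%.
- False positives in the direction of benefit only (2.5% each), independent tests: 1 − 0.975⁵ = 11.9%.
- Two-sided with a common correlation between test statistics (simulation, 400,000 draws; the article gives no correlations, so these are assumed):

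| Assumed correlation | At least one rejection in five |
|---|---|
| 0 | 22.6% |
| 0.3 | 20.9% |
| 0.5 | 18.4% |
| 0.7 | 14.8% |
| 0.9 | 10.1% |

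- If the two event outcomes were so rare that their tests almost never rejected, about three tests would remain. Under independence that gives 1 − 0.95³ = 14.3% two-sided, or 1 − 0.975³ = 7.3% in the direction of benefit.

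**3. Power if all five stayed primary with alpha split equally.** Each test would have alpha 0.05/5 = 0.01. For HbA1c, with a standardised difference of 6/9 = 0.667 (t-test):

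- 37 evaluable per group: 58.9%.
- 50 evaluable per group: 75.8%.
- For 80% power: 54.2, so 55 evaluable per group.

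The planned 50 per group would miss 80% even with no dropout. The 37 corresponds to a loss of 1 − 74/100 = 26%, which is implied by the totals and not stated.

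**4. Other sections compared with the five-part label.** The Clinical variables section lists HbA1c, time in range and time below range among the data to be collected, but neither severe hypoglycaemia nor ketoacidosis. The between-group tests named are for interval, ratio and ordinal data, with none specific to event outcomes. The Discussion's list of hoped-for improvements also leaves the two events out. The rest of the article thus does not treat all five as equal primary outcomes.

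**The case against.** The strongest reply is that HbA1c was plainly meant. It is listed first, it alone is powered, and the statistics section uses the singular. On that reading the other four only describe a glycaemic-control domain. This is the likely intention, and it supports the proposed fix, but no section says it and the outcome list says otherwise.

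A second reply is that this is a journal article, and that alpha allocation and testing order are commonly left to a full protocol or SAP that is not shown. That stands. A reader might infer that the trial has no control of its error rate, but the article cannot show that, and a missing multiplicity rule is not a finding here. The labels are a different matter. A testing rule elsewhere would not remove the conflict between the objective and the outcome list in this document.

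Several other tempting inferences also go too far:

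- **That success on any one measure is the written criterion.** No section states it. If all five had to succeed, alpha would be controlled, but 80% would no longer describe the trial's chance of success.
- **That 22.6% is the chance of falsely claiming benefit.** It counts rejections in both directions under independence. The benefit-direction figure is 11.9%, and positive correlation or conservative tests on rare events would lower it.
- **That seven outcomes are in play.** The article does not give that count. Satisfaction uses two questionnaire versions, one of them collected only at 12 or 18 months, and the health scale covers several areas.
- **That the 80% power statement is wrong.** It is valid marginal power for HbA1c at 0.05 and fails only if alpha is split.

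**Conclusion.** The point holds as a defect of definition: as this document fixes it, the trial has no single primary endpoint. The outcome list names five measures, the power calculation serves one, and two domains are primary in the aim but secondary in the outcome list. These contradictions are in the text and rest on no assumption.

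The size depends on how the gap would be filled. If any one of five sufficed, the two-sided false-positive rate would be at most about 23%, and about 10% to 21% for assumed correlations of 0.9 to 0.3. The 37 per group needs no correction while HbA1c is the sole primary outcome. An equal split of alpha over five outcomes would cost HbA1c about 22 percentage points of power with 37 per group (80.8% to 58.9%) and about 15 with 50 (91.0% to 75.8%).

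**What to change.** - In Participants and recruitment, name HbA1c at 6 months as the single primary outcome. This matches the power calculation and the planned 6-month comparison.
- Reclassify time in range, time below range, severe hypoglycaemia and ketoacidosis as secondary or safety outcomes.
- List treatment satisfaction and quality of life as secondary throughout. Align the abstract and Study aim with that, and the restated aim in the Discussion.
- In Statistical analysis and power calculation, name HbA1c where the primary endpoint is mentioned.

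If the sponsor prefers to keep several primary outcomes, the protocol should state the rule for combining them and the sample size should be recalculated.

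The cost of the main route is a wording change, with no added participants or visits. The downside is that the other outcomes can no longer support a stand-alone confirmatory claim. The article gives no power calculation for any of them.

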### Randomisation

After participants are identified, they will be randomised to an intervention group or a wait-list control group using closed randomisation envelopes containing randomisation cards. The closed envelopes have been developed by a person who is not involved in the inclusion or care of the patients.

All material is coded with consecutive digit code. The study manager will complete sealed envelopes containing randomisation cards. The nurses in the clinic will be responsible for the inclusion, randomisation, and the interviews. All personnel in the clinic will be informed about the study and trained to include subjects, collect data and the procedures to be conducted at each visit. The envelopes will be numbered from 1 to 100. The hospital staff will then take the top envelope when including a patient. All data will then be collected by existing staff at the relevant hospital. All material is coded with consecutive digit code. The code list is stored in a locked fireproof cabinet. A flow chart of the study is shown in Suppl. 1.

### Intervention

Baseline data will be collected for both groups before randomisation. The intervention group will be offered access to the virtual clinic instantly, and the wait-list control group will be offered the intervention after 6 months. At the 6-month follow-up assessment, a second data collection will be carried out for both groups (intervention and the wait-list groups). The intervention group will then continue with the intervention while the wait-list control group starts the intervention. The third data collection point for both groups will be after 12 months. Finally, data at 18 months will be collected for the wait-list group (after having access to the virtual clinic for 12 months).

Participants who meet the inclusion criteria will be randomly offered the chance to take part in the virtual clinic either immediately or after 6 months. Vista Dialog offers a digital service specially designed to facilitate continuity of care between diabetes patients and their nurses or doctors.

Vista Dialog supports a way of working that allows more frequent communication when needed, whilst allowing continuity of care and minimal disturbance to daily life. It provides additional access to healthcare without over- burdening health care professionals. For users, the virtual care increases the feeling of being in control and is easy to use and understand. The ability to provide instantaneous feedback means a more effective evaluation of health care interventions is possible. The simple method of facilitating further discussion contributes to an increased participation in the care which means that any potential problems or obstacles are discovered more quickly. Vista Dialog complements the usual care at the outpatient clinic and other eHealth services.

The virtual package/care consists of a platform partly delivered via a mobile application for patients and partly through a web interface/portal for staff. There is a secure log-in via a bank id system for patients and a secure login card for staff. Vista Dialog was developed in close collaboration with young people with diabetes and the platform allows both parties to easily communicate in real time via text messages. In addition, patients can book an online appointment with the Diabetes Specialist Nurse in times made available by the nurse via the application. It is also possible to start a spontaneous video meeting if a need arises in connection to a text message chat between patient and nurse. Documents or photos can easily be shared by patient or caregiver in the platform. Data from proximal technology (insulin pumps and CGM) is uploaded by the patient and can be reviewed and discussed in collaboration. Patients and caregiver have simultaneous access to data in platforms such as Diasend® or CareLink®. All together this invites and enables the patient to put forward their needs in the moment they arise. That contrasts to the conventional clinic where the patient needs to wait for a telephone consultation or the booked consultation in the future. Participants are well informed that the virtual clinic is not intended for very acute cases, such as ketoacidosis, and that the caregiver is only available during daytime weekdays.

### Measures and data collection

All data will be collected in-person at the diabetes clinic (clinical variables and psychometric measures). Outcomes measurement will be completed at baseline, 6 months, 12 months, and after 18 months in the wait-list group (control group).

#### Clinical variables

Glycosylated haemoglobin (HbA1c) as an indication of glucose control. Measure time in range (3.9–10 mmol/L) and time below range through Continuous Glucos Monitoring (CGM) /Flash Glucose Monitoring (isCGM) [19].Insulin requirements/dosage to explore changes as a further indicator of glycaemic control, as missed doses are common [11]. At the standard clinic appointments, insulin dosage will be downloaded using diabetes management software (e.g. Diasend®).The total daily insulin dose will be recorded where possible.Type of treatment to describe if the patient uses multiple daily injections (MDI) or continuous subcutaneous insulin infusion (CSII).Diabetes duration and age at onset of diabetes (data collected at baseline).Sociodemographic data to describe gender, age, living at home/independent living and level of education (data collected at baseline).

#### Psychometric measures

Diabetes Treatment Satisfaction Questionnaire: status version (DTSQs) and Diabetes Treatment Satisfaction: change version (DTSQc) (data collected after 12-months in the intervention group and after 18-months in the wait-list group (control group) (Information about DTSQs and DTSQc available at www.healthpsychologyresearch.com)Check Your HealthQualitative interview

